# Secondary traumatization in refugee care—EMDR intervention for interpreters (STEIN): a study protocol for a quasi-randomized controlled trial

**DOI:** 10.1186/s13063-024-08480-4

**Published:** 2024-10-01

**Keywords:** Secondary traumatic stress, Interpreters, Refugee care, EMDR

## Abstract

**Background:**

By the end of 2022, more than 100 million people worldwide fled their homes. Before, during and after their flight, refugees have high risk of experiencing traumatic events. Accordingly, around every third refugee is affected by posttraumatic stress disorder. For adequate mental health care, the service of interpreters is often urgently needed to overcome existing language barriers. However, repeated exposure with details of traumatic narratives, as experienced by interpreters, can be burdensome and can lead to trauma sequela symptoms in terms of secondary traumatic stress. Only few studies have examined the treatment of secondary traumatic stress to date. Based on the recommendations for the treatment of posttraumatic stress disorder with confrontational methods, this study was designed to evaluate the effectiveness of an eye movement desensitization and reprocessing (EMDR) intervention in a sample of interpreters working in refugee care suffering from secondary traumatic stress symptoms.

**Methods:**

To evaluate the effectiveness of an EMDR intervention for the treatment of secondary traumatic stress symptoms, a quasi-randomized controlled trial using a waiting group design will be performed. Participants will be treated with a maximum of 6 sessions based on EMDR standard protocol. Primary outcome is the symptom load of secondary traumatic stress, assessed with the Questionnaire for Secondary Traumatization, while secondary outcomes comprise further symptom complexes such as PTSD due to self-experienced traumatic events, depression, anxiety, and somatization as well as quality of life, quality of professional life, and psychological wellbeing that will be assessed with the PDS, PHQ-9, GAD-7, SSD-12, SF-12, PROQOL-5, and WHO-5, respectively.

**Discussion:**

Our primary interest is to determine the efficacy of an EMDR intervention in interpreters affected by secondary traumatic stress, especially how many sessions are needed for significant symptom reduction. Change of associated symptom complexes and quality of life will be investigated. Reprocessing one’s own stressful experiences may also contribute to this, which is not the focus of the treatment but relevant to the EMDR protocol. This study aims to assess if EMDR could be an acceptable, effective, and time-efficient method for reducing work-related secondary traumatization.

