### Primary outcome measure

The questionnaire-based data collection will be carried out upon the initial screening appointment (T1) for each group. For the intervention group, the second data collection point (T2) is around 6 weeks after T1, after the last session for the intervention, then 4 weeks (T3) and 8 weeks (T4) after T2. For the waitlist control group, T2 will be 6 weeks after T1, then after their last session (T3) and 4 weeks (T4) after T3. Also see Fig. 1. The participants will receive the link to the online questionnaires as well as reminders, if necessary, by email.

Secondary traumatic stress will be surveyed with the Questionnaire for Secondary Traumatization (“Fragebogen zur Sekundären Traumatisierung,” FST) [31]. This questionnaire surveys different symptoms of secondary traumatic stress based on diagnostic criteria of DSM-V for posttraumatic stress disorder, such as rumination, intrusions or nightmares, avoidance behavior, and, furthermore, cognitive or behavioral changes. The frequency of the above symptoms in the last week is assessed by 31 items on a 5-point Likert scale (1 = never, 5 = very often). From a sum score of ≥ 65, moderate secondary traumatic stress can be assumed. The structure of the questionnaire is similar to the Impact of Event Scale [40] and is designed to be used in professional context. It showed good internal consistency for the total score (Cronbach’s *α* = 0.94) in three different samples of professionals.

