### Intervention

Participants will be allocated to a therapist, medical doctor or psychologist of the department who will have completed, at least, EMDR training level 1. The EMDR treatment that will be carried out is comprised of 8 phases according to Shapiro [51]. In the first session, phases 1 and 2 will be conducted. The first phase includes the establishment of a therapeutic relationship as well as the exploration of the symptomatology and the trauma history. In this case, the therapist will comprehensively examine the symptoms of secondary traumatization including distressing situations relating to their work in refugee care in the present. Emotion regulation strategies of the participant will be elaborated. With help of the “adaptive information processing” model (AIP), the therapist and the participant will work out underlying stress situations from the professional context. According to the AIP model, traumatic memories, but also other “live events” or disturbing experiences that do not accord to the trauma criteria, can create a “pathogenetic memory.” These pathogenetic memories are stored in a dysfunctional way, are not connected to adaptive memory networks, and, subsequently, cause symptoms. Based on this assumption, repeated exposure to details of refugees’ traumatic experiences leads to dysfunctional storage of this experience of the affected interpreters [52, 53]. The therapist and the participant will carve out the respective distressing situations and classify them on a scale from 0 to 10 (subjective level of disturbance, SUD), as stated in the EMDR manual. Additionally, the participant will be introduced to the EMDR technique itself. An imaginative exercise, “safe place,” will be executed together and reinforced with EMDR technique. Techniques to stop flashbacks will be discussed. Additionally, the participant will receive a further imagination exercise, called “safe exercise,” that helps distancing oneself from disturbing thoughts. The first session takes 50–60 min. Phase 3–7 will be conducted in the following sessions according to the EMDR standard protocol. Phase 8 will be performed at the beginning of every exposition session. The EMDR standard protocol will be applied. This means that the disturbing memories will be worked on in a specific (“the first, the worst, the last”). However, by mutual agreement, the order in which the stressful memories are processed is left open to the therapist and the participant, if this leads to greater openness to therapy and adherence. Sessions will take place once a week; the therapist and participant will agree mutually on the date of the sessions, and they can be adapted to the participants’ needs. The confrontational sessions ends ideally when the SUD is 0. However, depending of the processed content, this cannot always be achieved, for example if the participant processes earlier stressful memories through so-called affect bridges. In this case, the session can be closed if SUD is not 0 but only reduced from the initial level. In this case, work on this memory will continue in the following session (phase 8). The processing time can differ between patients and takes around 60–90 min. A maximum of six sessions will be conducted. The number of sessions will be adapted to the participants needs. This implies that within the span of these six sessions, the stressful situations related to the participant’s work with refugees, which the participant seeks to address, are systematically managed. If a complete reduction of the SUD is not achieved within a single session, the issue may be resolved over 2–3 sessions. However, it is generally expected that each session is self-contained, as the nature of the underlying stressors suggests that a full reduction in SUD can be accomplished within one session. Consequently, the number of sessions corresponds to the number of specific situations requiring attention. Conducting fewer than six sessions does not imply that any therapeutic content is omitted. Participants in both groups receive the same intervention.

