## Discussion

In this study, the effectiveness of EMDR intervention in interpreters working in refugee care who are suffering from symptoms of secondary traumatization will be evaluated. The effect on further symptomatology as well as quality of life, quality of professional life, and psychological wellbeing will be evaluated.

EMDR is an effective approach to reduce posttraumatic stress symptoms and is one of the recommended treatments for PTSD [23, 62–64]. However, the primary target of “pathological memory” that will be processed is not self-experienced traumatic events but traumatization through exposure with traumatic details of the refugee’s narratives and empathetic indirect experiencing. It is known that there is a positive correlation of having directly experienced traumatic events and of developing symptoms through secondary traumatization [9]. In a sample of interpreters working in refugee care, 58% experienced traumatic experiences themselves [17]. In EMDR treatment, potential linkages between the secondary traumatic stress and the interpreter’s potential own distressing or traumatic experiences can be activated through the reprocessing. Reprocessing potentially underlying stressful experiences is inherent in the EMDR protocol and could also affect the parameters examined. For the present study, several points of interest will be examined. Firstly, it is crucial to assess whether this type of structured and targeted treatment offer meets the needs of those affected and is subsequently utilized. Furthermore, the study aims to determine the number of sessions required to achieve a significant symptom reduction. EMDR has the potential to be an effective and time-limited intervention for the treatment of work-related secondary traumatization. If the assumption is confirmed, further studies could be carried out in other target populations affected by secondary traumatic stress. Additionally, the effect of emotional bridging to address related personal traumatic experiences will be investigated. Instead of being quantifiable, these results will be observed and stated descriptively after being seen during therapy sessions.

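### The stated aim of finding how many EMDR sessions are needed cannot be met: no FST is taken during treatment and session number follows need and progress

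*Protocol article*

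**What the plan says.** The aim appears twice in the protocol article. The Discussion paragraph of the Abstract names efficacy as the primary interest, "especially how many sessions are needed for significant symptom reduction". The Discussion section says that "the study aims to determine the number of sessions required to achieve a significant symptom reduction".

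The Primary outcome measure section fixes when the FST is taken. For the intervention group, after T1 at screening, "the second data collection point (T2) is around 6 weeks after T1, after the last session for the intervention", with T3 and T4 four and eight weeks after T2. For the waitlist group, "T2 will be 6 weeks after T1, then after their last session (T3) and 4 weeks (T4) after T3".

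The Intervention section sets the number of sessions: "The number of sessions will be adapted to the participants needs", up to a maximum of six. It adds that "the number of sessions corresponds to the number of specific situations requiring attention", and that one issue may take two to three sessions if the SUD rating is not fully reduced in one.

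The Statistical analyses section contrasts whole periods (treatment, follow-up, waiting). Its covariates are psychiatric treatment, psychopharmacological medication and personal traumatic experience; number of sessions is not among them.

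**The concern.** To say how many sessions are needed, one needs either the outcome measured as sessions accumulate, or groups assigned to different numbers of sessions. This design has neither. All that remains is to compare people who ended with different session counts, and the count is itself produced by how much a person had to process and how quickly it resolved.

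At stake is a published statement that a given number of sessions is required or sufficient. Readers could use it to plan services, although it would mainly describe who needed more or less treatment.

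**Working it through.** **The plan's own figure.** The sample size is 34, from a repeated-measures ANOVA with d = 0.5, α = 0.05 and power 0.8. Take f = d/2 = 0.25, two groups, m = 2 measurements and a correlation ρ = 0.5 (an assumption; the article gives none). Then λ = f²·N·m/(1−ρ) = 0.0625 × 34 × 2 / 0.5 = 8.5 and the power is 0.807, so 34 is reproduced. It is sized for the EMDR-versus-waitlist contrast and says nothing about the session question.

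**FST measurements relative to treatment** (Primary outcome measure):

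| Group | Before first session | Between first and last session | After last session |
|---|---|---|---|
| Intervention | T1 | none | T2, T3, T4 |
| Waitlist | T1, T2 | none | T3, T4 |

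No within-person course of FST by session can be drawn in either group. The SUD is rated during therapy, but for individual distressing situations. It does not measure overall FST symptom load, and the article names it neither as an outcome nor in the analysis.

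**What determines the number of sessions** (Intervention): the participant's needs, the number of situations, and whether SUD has fallen far enough. The first two reflect burden at entry and the third reflects response. The alternating allocation described under Randomization assigns immediate or delayed treatment, so it does not balance people across session counts.

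**Direction of the bias.** Two mechanisms pull in opposite directions:

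- If fast responders stop early, those with many sessions can show less change.
- If people with higher baseline burden have more situations and also more room to improve, those with many sessions can show more change.

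A simulation shows how far the first alone can go. Its values are assumed and not from the article: a mean gain of 5 FST points per session after the preparatory one, between-person SD 2, and sessions continuing until a 15-point gain or the cap of six. Every session helps, yet the regression slope of FST change on sessions is +1.8 points per session, so more sessions look worse. With sessions assigned at random (2 to 6) and a gain of 5 points per session for everyone, the slope is −5.0. This shows that the sign can reverse; it does not predict that it will.

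**Precision.** Expected completers: 40 × (1 − 0.18) = 32.8, about 33. The article gives no distribution of session counts, so assume an even spread.

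| Range of sessions | People per count | 95% half-width for mean change, normal quantile |
|---|---|---|
| 3 to 6 (Methods/design) | 33/4 = 8.25 | 1.96/√8.25 = 0.68 SD |
| 2 to 6 (analysis-set minimum to cap) | 33/5 = 6.6 | 1.96/√6.6 = 0.76 SD |

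If each count's SD is estimated from its own members, the t quantile widens this: with 7 people, 2.447/√7 = 0.92 SD of change. An uneven spread would leave some counts with fewer people. These widths exclude the confounding.

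**The case against.** The strongest reply is that the session question stands outside the tested plan. The hypothesis in the Background, the research question in Methods/design, the sample size and the model all concern EMDR against waitlist. Moreover, the Intervention section treats until the chosen situations are managed and says that stopping short of six omits no content. On that rule, the number of sessions received is a usable descriptive answer, limited by the cap.

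Both points stand and shape the remedy, but they do not remove the problem. The two aim statements tie the number to a significant reduction in symptoms, which a count of sessions used does not show. Nor is this a detail left to an analysis plan that is not shown: no analysis plan can supply unmeasured FST values or undo a session number that depends on burden and response.

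A reader might infer more than the article supports:

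- That participants with more sessions will look worse. This is plausible for the final score but not established for change from T1. The simulation's stopping rule is invented, and the Intervention section generally expects one session per situation, with carry-over as the exception.
- That the time-efficiency question depends wholly on this aim. A benefit over waitlist within at most six sessions would itself bear on it.
- That the FST is taken only once on each side of treatment. There are four time points per participant; the gap is during treatment.

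**Conclusion.** The point holds as a mismatch between a stated aim and the design. There are no FST values during treatment in either group, session number is not assigned, and no analysis term addresses it. Any comparison by sessions received is confounded by burden and response in an unknown direction. It would rest on about 7 to 8 people per session count, with half-widths of roughly 0.7 to 0.9 SD of change, assuming 18% dropout from 40 and an even spread. The core conclusion does not depend on those figures.

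A reader might take this as a flaw in the efficacy comparison. It is not: the EMDR-versus-waitlist contrast in FST change does not use session number and is unaffected by this point. The change should be made before results are reported.

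**What to change.** In the Abstract's Discussion paragraph and the Discussion section, replace the aim with a descriptive one, for example: *We will describe the distribution of sessions received, the SUD rating by session, and FST change by number of sessions received. The last is descriptive and non-causal and does not estimate how many sessions are required.* Draw no conclusion about a required number. Confirm that session counts and SUD ratings enter the study data, and reconcile the session ranges first: a maximum of six in the Abstract and Intervention, three to six in Methods/design, at least two for the analysis set. The rewording is free and can be done at any recruitment stage.

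Optionally, if the sponsor accepts the burden, send the FST weekly through the existing online survey between T1 and T2 in both groups. Its recall period fits: "The frequency of the above symptoms in the last week is assessed by 31 items". Report the EMDR-waitlist difference by week since allocation in all allocated participants, including those whose sessions have ended. Present it as time to benefit and not as sessions required, because session dates are flexible and week does not equal session. The cost is about 5 × 31 = 155 extra items per person, in a trial that already names participant numbers as a possible limitation. It would also come mid-trial: recruitment had begun at submission and was expected to finish around June 2024, so this option may no longer be open.

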**Trial registration:**

German Clinical Trials Register, DRKS00032092, registered 16 June 2023.

## Background

In 2022, more than 100 million people worldwide had fled their home or place of origin due to war, natural disasters, or the consequences of poverty [1]. Of these, more than 6 million people were from Ukraine alone [2]. It is commonly known that the prevalence of mental illnesses of refugees and asylum seekers is far higher than in the general population due to stressors occurring pre-, peri-, and post-flight [3–5]. In particular, posttraumatic stress disorder (PTSD) affects around 30% of the refugee population [3]. However, the number of people having exposed traumatic events is assumed to be substantially higher [6, 7].

Mental health care of refugees largely depends on the availability of interpreters, as, especially in the early post-migration phase, the language barrier is a significant barrier in implementing adequate mental health care. During interpreters’ work, interpreters are often confronted with personal narratives of refugees, including traumatic events. Empathetic listening gives rise to a simultaneous experience of vivid imagination and somatosensory sensations. These narratives can affect the listening person but can also be extremely burdensome. This empathic compassion can even result in symptoms similar to posttraumatic stress disorder that are comprised of intrusions, avoidance behavior, hyperarousal, and alteration of cognition and mood even though the event was not personally experienced. This phenomenon is described as secondary traumatization [8]. The risk to develop symptoms of secondary traumatic stress can increase not only by the quantity of reports of traumatic events but also by the way in which the experience is narrated [9, 10]. Similar concepts that overlap with secondary traumatic stress are compassion fatigue that is characterized by feelings of helplessness, psychological and emotional exhaustions [11], and vicarious traumatization that includes a permanent change in cognitive schemas and beliefs [12]. To take this into account, the diagnostic criteria for post-traumatic stress disorder have been adapted in the DSM-V: in the recent version, “experiencing repeated or extreme exposure to aversive details of the traumatic event(s)” is also sufficient as an A-criterion [13]. In ICD-10 and ICD-11, on the other hand, a traumatic event is defined as an event of “extremely threatening or horrific nature,” that is directly experienced or witnessed [14], and thus rather broad, which stems from the observation that PTSD symptoms can develop after experiencing a traumatizing event of any kind and that the definition of a traumatic event is therefore not decisive [15]. Research has shown that PTSD symptoms can develop after secondary traumatization, but to a lesser extent [16]. However, an independent diagnosis for symptomatology due to secondary traumatization cannot be found in either of the two diagnostic manuals.

Regarding the prevalence of secondary traumatic stress, Kindermann et al. [17] showed that in a sample of interpreters working in refugee care, 21% are affected by trauma sequela symptoms due to secondary traumatization, and around 6% show high symptom scores. However, this is not the only population that can be affected by secondary traumatization. Secondary traumatic stress is particularly prevalent among trauma therapists and other caregivers of traumatized clients [8, 18], nurses [19], or first responders [20] as highlighted in various studies.

However, despite the traumatic stress burden resulting from working with traumatized patients, the knowledge about effective treatment is rather scarce. In a systematic review on the treatment of secondary traumatic stress among mental health workers conducted by Bercier and Maynard in 2015 [21], none of the selected studies met the inclusion criteria. The authors concluded that insufficient attention had been given to the distinction of existing concepts and the evaluation of the necessity for large-scale intervention in the field. This gap was attributed to the ongoing development of research, which primarily focused on genesis and clinical presentation. In 2012, Sprang et al. [22] presented an overview of the current state of knowledge as well as the challenges with regard to the research field of secondary traumatic stress. With regard to therapeutic interventions, they showed that various symptom-related approaches have been published, such as psychoeducation, emotion regulation training, or mindfulness training. With a view to improving interventions for secondary traumatic stress, two different approaches for further research were recommended: the amelioration of preventive interventions and specific interventions for affected workers.

Due to symptoms having a clinical similarity to posttraumatic stress disorder, it is suspected that interventions based on therapeutic approach for PTSD can be equally effective for secondary traumatic stress [22]. In national and international guidelines, exposition therapy approaches as first line treatment for posttraumatic stress disorder are recommended [23–27]. Among others, eye movement desensitization and reprocessing (EMDR) is a validated and effective treatment for PTSD [28]. While the underlying effect of bilateral eye stimulation is not fully understood [29], there is large evidence of EMDR effectively reducing symptoms of traumatic stress [30]. The planned study will examine the effectiveness of EMDR on secondary traumatic stress symptoms in a sample of interpreters working in refugee care. Therefore, a quasi-randomized controlled trial will be conducted, with a waitlist-control group to compare the development of symptoms of secondary traumatic stress in each group with and without EMDR intervention. The aim is to examine the hypothesis that EMDR intervention significantly reduces symptom burden of secondary traumatization compared to waitlist control.

